**Procedures**								
	Written informed consent	X^a^	—^b^	—	—	—	—	—	—
	Entry criteria assessment	X	—	—	—	—	—	—	—
	Participant demographics	X	—	—	—	—	—	—	—
	Group session (intervention or wait-listed control)	X	—	—	—	—	—	—	—
	Facilitator process notes	—	—	—	X	X	—	—	—
	Sexual health self-efficacy and capacity	—	X	X	—	—	X	X	X
	Mental health	—	X	X	—	—	X	X	X
	Internalized queerness	—	X	X	—	—	X	X	X
	Coping	—	X	X	—	—	X	X	X
	Hope	—	X	X	—	—	X	X	X

^a^Procedure conducted.

^b^Not applicable.

### Sample Size

Approximately 300 participants will participate in AFFIRM. Each CCAS has agreed to complete a minimum of 1 AFFIRM iteration, comprising 1 intervention group and 1 wait-list group. This sample was primarily determined to assess the implementation-based outcomes. In addition, this sample would be sufficient for analysis of exploratory objectives, as described below.

### Recruitment

Potential participants are recruited in multiple ways (1) via CCASs and other local community organizations (which are provided with flyers and cards directing potential participants to the independent Web-based screening); (2) via emails to local organizations and community groups serving SGMY (which are provided e-versions of the flyers and cards); and (3) Web-based postings on Facebook and Instagram. The Web-based postings involve geographically and demographically targeted *paid boosts* using Facebook’s Ad Manager.

### Data Management and Monitoring

Data are downloaded from Qualtrics, cleaned, and saved as password-protected files on an encrypted research drive. After data collection and cleaning for the entire study is completed, the data will then be deleted from Qualtrics servers. A data monitoring committee is not required at this stage, as the current phase is primarily focused on implementation acceptability in community sites; however, one will be formed before instigation of a larger trial.

### Harms

As a psychosocial study, risks for adverse effects are negligible or nonexistent. The study’s distress plan, discussed above, will be used if participants present in crisis.

### Ethics and Dissemination

This study has been approved by the University of Toronto’s HIV/AIDS Research Ethics Board (protocol ID#35229). As an uncontrolled, nonrandomized trial, registration at this stage was not completed. If this implementation stage proves promising and the study proceeds to a full-scale multicenter trial, a new protocol will be registered and submitted for publication before participant enrollment.

## Results

It is anticipated that data analyses will use effect size estimates, paired sample *t* tests, and repeated measures linear mixed modeling (LMM) using SPSS to test for differences pre- and postintervention [112-114]. Descriptive analyses will summarize data and profile all variables, including internal consistency estimates. Distributional assumptions, univariate, and multivariate normality of all variables will be assessed. Data determined to be missing at random will be imputed with the expectation-maximization method with importance re-sampling [113].

Clinically significant change estimates and repeated measures LMM will be used to compare the influence of participation in AFFIRM to wait-list on sexual health self-efficacy and capacity, internalized queerness, hope, and depression of SGMY [114]. To test the influence of intervention on multiple outcomes, LMM using both time and interaction terms will be fit using SPSS [115,116]. Repeated measures LMM is considered an improvement over classical repeated measures analyses (eg, repeated measures analysis of variance) because of frequent correlated errors and nonindependence of observations that are forbidden by the assumptions of standard general linear approaches [114-116]. LMM also allows for the exploration of time effects, which is a potential source of confounding because of the partially randomized nature of the design and assumption of no interaction between intervention effects and time [117]. A total of 2 mixed models will be constructed to test the relationship between the intervention condition (AFFIRM group or the treatment as usual or wait-list [TAU/WL] group) and change in outcome variables from pre- to postintervention. Model 1 will include time and condition and will indicate whether there is a significant change in outcome variables over time and if significant cross-sectional associations between treatment condition and outcome variables exist. In model 2, interaction terms will be added to assess the longitudinal associations between treatment condition and the change (slope) of outcome variable scores from pre- to postintervention. The interaction of multiple intersecting identities as well as site, group, and individual-level covariates will be included in this analysis. The impact of behavioral interventions also can be identified through effect size [114]. The potential clinical significance of AFFIRM will be assessed by calculating Cohen *d* effect sizes, comparing percentages of participants at 2 time points. It is expected that compared with the TAU/WL group, the AFFIRM group will show statistically significant change in hypothesized outcomes. The use of similar sample sizes with multiple time points and measures is considered appropriate [112] and allows for analysis of change effects using data points. The qualitative data collected through the acceptability measures will be analyzed using content analysis with ATLAS.ti software by a minimum of 3 coders [118].

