
### Research Questions, Hypotheses, and Objectives

This project is intended to scale-up implementation and delivery of AFFIRM, an 8-session manualized group coping skills intervention focused on reducing sexual risk behaviors and psychosocial distress among SGMY. This project aims to decrease sexual risk taking, depression, and internalized homophobia and increase levels of sexual self-efficacy and proactive coping among SGMY (ages 14-29 years). This project has the following research questions:

To what extent can AFFIRM be feasibly implemented in a range of practice settings, such as community health centers, family health teams, and community-based organizations?What are the facilitative conditions and implementation barriers to effective delivery of AFFIRM?How does participation in an affirmative coping skills intervention (AFFIRM) impact the psychosocial distress and sexual self-efficacy of SGMY?

Given these research questions, the study has the following hypotheses:

Hypothesis 1: AFFIRM can be feasibly implemented in a range of practice settings, and SGMY will have high rates of acceptability of the intervention.

Hypothesis 2: SGMY participating in AFFIRM will show significantly greater decreases in psychosocial distress (eg, internalized stigma and depression) compared with wait-listed controls (ie, SGMY attending existing community programs).

Hypothesis 3: SGMY participating in AFFIRM will show significantly higher levels of sexual self-efficacy and coping compared with wait-listed controls.

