#### Trial Design

This pragmatic quasi-experimental study uses a stepped wedge wait-list crossover design (SWWCD), whereby all participants receive the intervention in clusters [94-98]. SWWCD has been utilized in community-based research where traditional randomization with a no-treatment condition is unethical, unacceptable to community stakeholders, or not feasible [98]. This study will examine the effects of participating in an AFFIRM intervention group (each consisting of 6-10 participants) compared with wait-list for SGMY (ages 14-29 years).

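### Paired pre-post t tests and a Cohen d on percentages are planned beside the wait-list-controlled mixed model with no stated role, so uncontrolled change can be read as evidence of efficacy

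*Protocol article*

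**What the plan says.** The opening sentence of the Results section lists the planned analyses together: "It is anticipated that data analyses will use effect size estimates, paired sample" *t* tests, and repeated measures LMM, all "to test for differences pre- and postintervention". Descriptive analyses come in a separate sentence, so the paired tests are not presented as descriptive.

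The next paragraph gives the controlled analysis: "repeated measures LMM will be used to compare the influence of participation in AFFIRM to wait-list". It describes two models. The first has time and condition. For the second: "In model 2, interaction terms will be added to assess the longitudinal associations between treatment condition and the change (slope) of outcome variable scores". It adds that intersecting identities, "as well as site, group, and individual-level covariates will be included in this analysis". Clinical significance is to be judged by Cohen d "effect sizes, comparing percentages of participants at 2 time points".

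Hypothesis 2 (Research Questions, Hypotheses, and Objectives) concerns decreases in distress "compared with wait-listed controls (ie, SGMY attending existing community programs"; Hypothesis 3 uses the same comparator. Trial Design describes a design "whereby all participants receive the intervention in clusters", with 6 to 10 participants per group. Participant Timeline adds a prewait survey so that the wait-list group's pretest can serve as the control follow-up.

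**The concern.** Hypotheses 2 and 3 ask whether AFFIRM does better than waiting. A paired pre-post test asks only whether AFFIRM participants changed. Natural improvement, regression to the mean in volunteers for a coping program, and repeated completion of the same surveys all count towards that change. The wait-list data collected to remove these influences do not enter the test. It also treats people who sat in the same group as independent, which makes its standard error too small if groups differ in how much they change.

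The clinical-significance figure has a separate defect. Cohen d is a difference in means divided by a standard deviation. It is not defined for two percentages, which call for a risk difference, an odds ratio or Cohen h. The sentence also compares two time points without naming a comparator.

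At stake is how the psychosocial results are read. The article does not say which analysis carries the efficacy inference, and its Ethics and Dissemination section calls the trial uncontrolled although a control group is planned. A significant paired test or a large pre-post effect size could therefore be taken as support for Hypotheses 2 and 3.

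**Working it through.** **Inputs from the protocol article.** About 300 participants; allocation about 2:1 and not randomized, so about 200 AFFIRM-first and 100 wait-list; groups of 6 to 10; all participants eventually receive AFFIRM. A paired test could thus use about 200 pairs (AFFIRM-first only) or up to 300 (wait-listed participants included after crossover).

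**Assumptions, because the article gives no figures.** Two-sided alpha 0.05; natural change 0.10 to 0.15 SD of the within-person difference; group ICC of change 0.02, 0.05 and 0.10; 8 per group (mid-range). The sample of 300 has no power calculation to reproduce; the article says it was set mainly for the implementation outcomes.

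**1. Paired test when AFFIRM has no effect.** Rejection rate ≈ Φ(d√n − 1.96), with d the natural change in SDs of the difference.

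- n = 200, d = 0.10: Φ(1.414 − 1.96) = Φ(−0.546) ≈ 29%
- n = 200, d = 0.15: Φ(2.121 − 1.96) = Φ(0.161) ≈ 56%
- n = 300, d = 0.10: Φ(1.732 − 1.96) = Φ(−0.228) ≈ 41%
- n = 300, d = 0.15: Φ(2.598 − 1.96) = Φ(0.638) ≈ 74%

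**2. Clustering alone, with zero mean change, in the paired test.** Design effect DE = 1 + (m − 1) × ICC with m = 8; true type I error = 2[1 − Φ(1.96/√DE)].

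- ICC 0.02: DE = 1.14, type I error 6.6%
- ICC 0.05: DE = 1.35, type I error 9.2%
- ICC 0.10: DE = 1.70, type I error 13.3%

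**3. The same clustering in the contrast with wait-list.** Waiting is not delivered in groups, so only the AFFIRM arm is taken as clustered. The variance of the contrast is proportional to DE/200 + 1/100, against 1/200 + 1/100 = 0.0150 without clustering.

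- ICC 0.02: 0.0057 + 0.0100 = 0.0157; SE ratio √(0.0157/0.0150) = 1.02; type I error if ignored 5.5%
- ICC 0.05: 0.00675 + 0.0100 = 0.01675; SE ratio 1.06; type I error 6.4%
- ICC 0.10: 0.0085 + 0.0100 = 0.0185; SE ratio 1.11; type I error 7.8%

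**4. Simulation of both features.** 25 AFFIRM groups of 8 against 96 wait-list participants, with an equal natural change of 0.2 SD in both arms, no AFFIRM effect and 3,000 runs per setting. At ICC 0, 0.05 and 0.10 the paired test rejected in 80%, 78% and 75% of runs. A simple comparison of change between arms, ignoring clusters, rejected in 5.3%, 6.3% and 6.9%.

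The missing control is thus the larger problem, and clustering the smaller one.

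**The case against.** The best defense is that the article already plans the right comparison. The LMM is assigned to AFFIRM versus wait-list, model 2 tests change by condition, and the stated expectation of significance is relative to treatment as usual or wait-list. The psychosocial outcomes are labeled exploratory; the primary outcomes are feasibility and acceptability. The Cohen d sentence may merely have run together effect sizes and the clinically significant change estimates, which the article says will be compared with wait-list.

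Most of this stands, and it limits the point. Three stronger readings are not supported:

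- A reader might infer that natural improvement *will* be reported as an AFFIRM effect. The article does not say that the paired tests decide Hypotheses 2 and 3, so one can say only that they may be read that way.
- A reader might infer that group enters the LMM as fixed indicators aliased with condition. The wording can equally mean covariates measured at site, group and individual level, and wait-listed participants contribute both waiting and AFFIRM intervals. The random-effects structure is also a detail that an article may leave to the analysis plan.
- A reader might carry the 6.6-13.3% type I error over to the wait-list comparison. Those figures hold for a fully clustered within-arm test; step 3 gives the smaller ones for the controlled contrast.

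What the defense does not answer is that the paired tests appear as tests, apart from the descriptive analyses and with no supporting role stated, and that Cohen d is specified on a quantity for which it is not defined.

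**Conclusion.** The concern holds in limited form and should be fixed. The paired tests cannot address Hypotheses 2 and 3. The 29-74% range in step 1 shows how easily they could reach significance with no AFFIRM effect, but it rests on assumed natural change, just as the clustering figures rest on assumed ICCs. The Cohen d defect needs no assumption: the statistic is wrong as worded.

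The exploratory status of these outcomes and the planned LMM keep this below a critical flaw. Nor does moving all inference to the LMM make the comparison causal: allocation is not randomized, so the model removes change common to both arms but not selection into them.

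**What to change.** - Name the model 2 condition-by-time term as the only test of Hypotheses 2 and 3, with a random effect of AFFIRM group on post-exposure records.
- Present paired pre-post changes descriptively, with confidence intervals and no significance tests.
- Define d as the LMM-adjusted AFFIRM minus wait-list difference divided by the baseline SD.
- Report percentages with clinically significant change as a risk difference versus wait-list, with a cluster-robust confidence interval.

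The cost is analysis wording only; data collection is unchanged. Confidence intervals for the controlled contrast become slightly wider: the SE is about 2-11% larger for ICC 0.02 to 0.10, with 200:100 participants, 8 per group and an unclustered wait-list.

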##### Allocation

Participants are allocated in an approximate 2:1 fashion to intervention: wait-listed control. This ratio is based on the availability of practice sites to implement AFFIRM in their clinical practices [96,97]. Importantly, similar to community programming, the groups are constructed to be developmentally appropriate. Participants in a particular intervention group are typically within an age range of 3 to 5 years. For example, a 14 year old would generally not be placed in a group with anyone older than 18 years. Groups of people aged between 18 and 29 years may have a broader age range, as developmental stage is not as relevant for established adults. AFFIRM also consists of mixed identity groups (eg, sexual identities and gender identities), based on community feedback. This means that a single intervention group could comprise SGMY from a range of identities. Many community organizations do not focus on 1 particular SGM subpopulation but instead serve all SGMY.

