#### Exploratory

Exploratory outcomes include changes in sexual health self-efficacy and capacity, mental health indicators, internalized homophobia, stress appraisal, proactive and active coping, and hope. These outcomes will be assessed through measures such as: the Sexual Health Capacity Scale [100], the Abstinence and Protection Self-Efficacy Scale [101], the Beck Depression Inventory-II [102], the Diagnostic and Statistical Manual of Mental Disorders-V (DSM-V) Self-Rated Level 1 Cross-Cutting Symptom Measure–Child [103], the Stress Appraisal Measure for Adolescents [104], the Brief COPE [105], the Proactive Coping Inventory for Adolescents-A [106], the Adult Hope Scale [107], the Internalized Homophobia Scale [108], the Current Mood Scale [109], the Everyday Discrimination Scale [110], and the LGBTQ Microaggession Scale [111] (see Table 1).

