### Participant Timeline

Table 2 shows the schedule of events. Participants complete a Web-based screening questionnaire, which includes their preferred site to participate in AFFIRM. For every 2 participants allocated to the intervention-only group, 1 participant is allocated to the wait-list group. The intervention-only group completes 4 data collection time points (pretest, posttest, 6-month follow-up, and 12-month follow-up). The wait-list group completes 5 data collection time points (prewait, pretest, posttest, 6-month follow-up, and 12-month follow-up). The prewait survey is completed immediately following their wait-listed control allocation, so that the pretest for the wait-list group serves as the follow-up on outcomes for the control group. Participants complete the pretests and posttests before the first week and at the last week of the intervention, respectively. The Web-based pretest is completed independently shortly before the first group session. The posttest is completed on tablets (eg, Android tablets) at the intervention location following the final group session. Participants complete the prewait (if applicable), the 6-month follow-up, and the 12-month Web-based independent follow-up. Participants are reminded to participate via email and provided the link to the survey. If participants do not participate following the initial email, up to 2 follow-up emails are sent as reminders for each time point. The follow-up emails are sent at 2 weeks and 4 weeks after the initial email (ie, every 2 weeks for 1 month). If participants indicated in their Web-based screening that SMS text message or phone call is their preferred form of communication, they also receive follow-up SMS text messages at 2 to 4 weeks after the initial email.

**Table 2 table2:** Schedule of events.

Visit details		Screening period			Study period (facilitator meeting; 8 weekly, 1-hour sessions)			Follow-up period	
Visit name		Screening survey	Prewait	Pretest	Orientation	Sessions 1-8	Posttest	6-month follow-up	12-month follow-up
Visit number.		−3	−2	−1	0	1,2,3,4,6,7,8	8	9	10
Week number		-8 to 0	-8 to 0	-8 to 0	0	1-8	8	32	56
Day number		−56 to 0	−56 to 0	−56 to 0	1-56	1-56	1-56	+224 to +238	+392 to +406
Visit window		±56	±14	±0	±0	±0	±0	±14	±14

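### Imputation is limited to data judged to be missing at random, but observed data cannot establish that; it should be a stated assumption with a sensitivity analysis

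*Protocol article*

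**What the plan says.** The missing-data rule is one sentence in the Results section: "Data determined to be missing at random will be imputed with the expectation-maximization method with importance re-sampling". The filled-in data would feed effect sizes, paired t tests and "repeated measures linear mixed modeling (LMM) using SPSS to test for differences pre- and postintervention". The comparison between conditions comes from the second mixed model, in which "interaction terms will be added to assess the longitudinal associations between treatment condition and the change (slope) of outcome variable scores".

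Three other sections bear on why scores may be missing:

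- **Discontinuation Criteria.** A participant found to be in crisis while attending AFFIRM in person leaves both the intervention and the study.
- **Participant Timeline.** The AFFIRM posttest is taken on a tablet at the site after the last session. The wait-list group's end-of-wait measure is its pretest, a web survey done alone shortly before its first session.
- **Participant Timeline, reminders.** "If participants do not participate following the initial email, up to 2 follow-up emails are sent as reminders for each time point". The 6- and 12-month surveys are also done alone on the web.

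The outcomes concerned are exploratory: "Exploratory outcomes include changes in sexual health self-efficacy and capacity, mental health indicators, internalized homophobia, stress appraisal, proactive and active coping, and hope".

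**The concern.** The sentence makes imputation depend on a finding that the data cannot supply. This is a rule the article states, not a detail left to an analysis plan that is not shown. Applied literally, it invites a test, most likely one of missing completely at random, whose result is then read as support for missing at random. The analysis would carry an assurance it has not earned.

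This matters because the protocol itself describes a route to missing scores that is tied to depression and mood. The crisis rule is written for in-person AFFIRM attendance, so in the pre-to-post comparison it can remove AFFIRM scores without a matching rule for the waiting period. If those scores are worse than the pretest would predict, the remaining AFFIRM scores look too good. Hypotheses 2 and 3 claim an advantage over the wait-list on these outcomes.

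**Working it through.** **No figure to reproduce.** The article gives no missing rate, standard deviation, alpha or standard error for these outcomes.

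**1. Can missing at random be determined?** Let x be the pretest and y the posttest, and let R show whether y is observed. Missing at random says that y given x and condition has the same distribution in those with and without a posttest. Suppose instead that the missing y are worse by δ standard deviations. Changing δ alters only unobserved values, so the likelihood of the observed data is the same for every δ. Missing at random is the case δ = 0, and no statistic from the observed data separates it from any other δ. A comparison of x between those with and without y can speak only against missing completely at random.

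**2. What is at stake if δ is not zero?** An analysis that assumes missing at random misstates each condition's mean by the missing share times δ, so approximately:

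overstatement of benefit = p(AFFIRM) × δ(AFFIRM) − p(wait-list) × δ(wait-list)

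If only AFFIRM departs, this is 0.1δ, 0.2δ, 0.3δ and 0.4δ at an assumed 10%, 20%, 30% and 40% missing. In the simulation below, the observed-data standard error at 30% missing was 0.106 to 0.128 standard deviations. A shift of one standard error then needs δ of 0.106/0.3 = 0.35 to 0.128/0.3 = 0.43.

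**3. Does the imputation method itself distort standard errors?** Inputs from the article: "Approximately 300 participants will participate in AFFIRM" and "Participants are allocated in an approximate 2:1 fashion to intervention: wait-listed control", giving 300 × 2/3 = 200 and 300 × 1/3 = 100. Assumptions not in the article: pre-post correlation 0.5 or 0.7, two-sided 5% level, no true effect, posttests missing at random given the pretest, no clustering, 1,500 runs per setting. With two time points, the time-by-condition test on complete or imputed data is a two-sample test on change. Multiple imputation used m = 20 sets pooled as T = W + (1 + 1/m)B. The observed-data analysis was a baseline-adjusted regression standing in for the likelihood model. Each cell gives mean SE / true SD, then type I error, over the two correlations.

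| Missing (assumed) | One expected-value fill-in | Multiple imputation, pooled | Observed data only |
|---|---|---|---|
| 10% | 0.91–0.92; 6.8–7.0% | 1.01; 4.7–4.8% | 1.00–1.01; 4.3–4.7% |
| 20% | 0.81–0.83; 10.3–11.0% | 0.99–1.00; 5.3–5.9% | 1.00–1.02; 4.7–4.9% |
| 30% | 0.72–0.74; 13.8–16.0% | 0.99; 5.1–5.6% | 0.98–1.00; 4.8–5.1% |
| 40% | 0.62–0.69; 17.5–22.9% | 0.97–1.03; 4.5–5.3% | 0.97–1.03; 4.1–6.1% |

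Simulation error at 5% is √(0.05 × 0.95/1500) = 0.6 percentage points, so the last two columns are consistent with 5%. A second simulation (baseline-adjusted comparison, correlation 0.6, 3,000 runs) gave 11.6%, 17.0% and 23.9% for a single fill-in at 20%, 30% and 40% missing. Over both simulations the range is roughly 10% to 24%.

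The inflation therefore comes from treating one fill-in as observed data. It does not arise with pooled multiple imputation or with observed data alone.

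**The case against.** **The wording may only be loose.** The sentence can be read as a prior judgement that missing at random is plausible. That is a fair reading, and if it is meant, calling it an assumption costs nothing. As printed, it is a condition for imputing.

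**The mixed model needs the same unverifiable assumption.** True. Moving to likelihood does not remove the assumption; it removes the pretence of having checked it. That is why the sensitivity analysis is needed.

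**Imputation still has uses.** This stands. A likelihood model handles missing outcome scores but not missing items within a scale or missing covariates, and paired t tests and percentages at two time points need both scores.

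**A reader might infer that standard errors will be too small.** The documents do not support this. The article never says the fill-in is done once. Importance re-sampling is a way of drawing imputed values, normally to make several data sets, so the wording points towards multiple imputation. The number of sets, the pooling and the imputation variables may be in an analysis plan that is not shown, and their absence is no fault.

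**Missing at random might still hold.** If crisis were well predicted by pretest scores in the model, the assumption could be adequate. The Data Collection section also allows some pretests on site, so the difference in survey setting is one of degree. The assumption is doubtful, not refuted.

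**The outcomes are exploratory.** This stands and limits the weight of the point. The primary outcomes are feasibility and acceptability, and the sample was set mainly for implementation outcomes.

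**Conclusion.** The rule cannot be carried out as stated, because missing at random cannot be established from the data collected. That conclusion needs no numerical assumption. The doubt about missing at random rests on the article's own crisis-withdrawal rule and on the different survey settings. The size of any bias is pδ, and the documents give neither p nor δ.

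Type I error of roughly 10% to 24% at an assumed 20% to 40% missing would arise only if a single fill-in were analysed as observed data. It is not a demonstrated error in this plan. The consequence is confined to exploratory outcomes, though Hypotheses 2 and 3 depend on them.

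**What to change.** 1. Delete the condition that data be found missing at random, and state missing at random as an assumption of the analysis.
2. Fit the planned mixed models by likelihood to all observed outcome scores, without first imputing missing outcomes.
3. Where imputation is kept (paired t tests, percentages at two time points, missing items or covariates), confirm that it is multiple and pooled, with condition in the imputation model.
4. Add a sensitivity analysis that shifts missing scores towards worse outcomes over a stated range of δ, with crisis withdrawals included among the missing.

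The cost is analysis wording and one extra run. Recruitment, data collection and the crisis procedure are unaffected; the procedure is cited only as a reason why scores go missing.
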